### Analysis plan for process measures

We are likely to include the following analyses to examine potential process variables. We will examine the degree to which participants develop automaticity by the habit index and the regularity of weighing assessed by their objective weighing scales and their association with weight change. Furthermore, we hypothesise that regular weighing induces participants to develop conscious cognitive restraint over their food intake and we will therefore assess the association between the frequency of weighing and the development of conscious cognitive restraint. As these are repeated measures we will use repeated measures mixed modelling. A Logic model will be developed and full mediation analysis will be undertaken using either Baron and Kenny’s approach or structural equation modelling.

The potential dose–response on the weight change at three and 12 months will be explored by including the frequency of self-weighing (average times per week) and its interaction with intervention arm in the mixed model analysis.

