### Assessments

#### Baseline

A researcher measures participant’s height and weight at a home visit before randomisation. Participants complete the baseline questionnaire and answer the open ended questions about their previous weight loss attempts and strategies they use to control their weight before being randomised. As a process measure the intervention group will be given a set of BodyTrace scales to use to weigh themselves, these scales transmit weight data to a remote database to provide an objective measure of weighing frequency (see below).

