### Process measures

We are collecting process measures to monitor recruitment, intervention delivery and potential variables that may mediate the outcomes. Our hypothesis is that self-weighing leads to the development of conscious cognitive restraint, which the National Weight Control Registry has found to be a key behavioural attribute associated with weight maintenance [17]. Using six items from the revised three factor eating questionnaire [16] we will examine if feedback from self weighing has led to development of conscious cognitive restraint of eating (measured in both groups) at three, six and 12 months post randomisation. In the intervention group we will use seven items from the index of habit strength [18] to measure the automaticity of self-weighing and five items from Steinberg [12] to measure perceptions of daily self weighing at the same follow-ups. At three, six and 12 months follow up participants in both groups will be asked to complete a series of open ended questions about any weight control practices they may have used in the previous two weeks, which will be coded. Within these questions we will specifically ask participants whether they have reapplied any behavioural techniques they acquired through participation in their weight loss programme and whether they have re-enrolled in a weight loss programme. We will then be able to examine whether the intervention may work by encouraging people to reapply lessons and techniques they learnt on the weight loss programme or it works by encouraging participants to enrol in a weight loss programme once more. Table 2 documents the process measures collected.

**Table 2 Tab2:** Measurements and study questionnaires at baseline and follow-ups

Reach		
Number of participants eligible		
Number of participants consented		
Number of participants consented and randomised		
Intervention		
	Comparator group	Intervention group
Frequency of recording self-weighing –record cards		X^a^
Frequency of self-weighing (objective scales)		X
Psychological Measures		
Index of habit strength [18]		X
Energy restriction [16]	X	X
Perceptions of self-weighing [20]		X
Thoughts about regular weighing (open ended questions)		X
Weight locus of control [21]	X	X
Weight loss strategies		
Weight control strategies (including frequency of self-weighing) [22]	X	X
Attendance at commercial weight loss programmes & application of skills learnt at weight loss programme (open ended)	X	X

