Open ended questions asked if participants are no longer managing their weight.	X	X
Intervention delivery of phone calls		X^a^

^a^3 month follow-up only

One weakness of previous trials is that self-weighing frequency was based on self-report rather than objective measures. Here we use Body Trace scales (http://www.bodytrace.com/) which use mobile phone signals to send the weight of the participant to a central database in real time. This will provide an objective measure of the weighing frequency of intervention participants and allow us to examine adherence to the daily weighing intervention.

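### The mediation plan permits Baron and Kenny's causal-steps method, which often misses real mediation if the weight effect falls short of 2 kg and gives no interval for the indirect effect

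*Protocol article*

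**What the plan says.** The section on the analysis plan for process measures opens tentatively: "We are likely to include the following analyses to examine potential process variables". It then names the method: "A Logic model will be developed and full mediation analysis will be undertaken using either" Baron and Kenny's method or structural equation modelling. It does not rank the two methods, and it does not list the variables that will enter as mediators.

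The Process measures section describes part of the data as "potential variables that may mediate the outcomes" and states the mechanism: "Our hypothesis is that self-weighing leads to the development of conscious cognitive restraint". Cognitive restraint is collected in both arms at three, six and 12 months. Table 2 marks questionnaire-reported frequency of self-weighing for both arms.

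Two other measures exist in the intervention arm only. For automaticity the text reads "In the intervention group we will use seven items from the index of habit strength". For the transmitting scales it reads "As a process measure the intervention group will be given a set of BodyTrace scales to use to weigh themselves" and "This will provide an objective measure of the weighing frequency of intervention participants". For these two, the Non-efficacy outcomes section and the process analysis plan speak of associations, with weighing frequency and with weight change.

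**The concern.** The classical causal-steps procedure is a chain of significance tests: arm on outcome (total effect), arm on mediator, and mediator on outcome given arm. Mediation is declared only if each is significant. The indirect effect is never estimated, so no interval shows how large or small it could be.

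The first link is the problem. A mechanism analysis is most informative when the main effect is modest, because it can then separate two explanations: weighing did not change restraint, or restraint did not change weight. Causal steps usually stops before reaching that question. A trial that used it could report no mediation when the data supported the pathway, and the theory behind the intervention would be judged on a test with little power.

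**Working it through.** **Inputs from the protocol article.** Sample size section: difference 2 kg, SD of weight change 6.3 kg, power 90%, significance level 5% (taken as two-sided; the text does not say), 280 per arm, 25% loss to follow-up. Pilot work section: intention-to-treat difference 0.7 kg.

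**Step 1. Reproduce the planned size.** n per arm = 2 × (1.960 + 1.282)² × 6.3² / 2² = 208.5, rounded up to 209. Allowing for loss, 209 / 0.75 = 278.7, rounded up to 279, or 558 in total. The article states 560, so its figure reproduces. Completers are 280 × 0.75 = 210 per arm.

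**Step 2. Power of the total-effect step.** The standard error of the difference is 6.3 × √(2/210) = 0.615 kg. Power = Φ(δ/0.615 − 1.96).

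| True total effect | δ/0.615 | Power of the step | Stops here |
|---|---|---|---|
| 0.7 kg | 1.14 | 21% | 79% |
| 1.0 kg | 1.63 | 37% | 63% |
| 1.5 kg | 2.44 | 68% | 32% |
| 2.0 kg | 3.25 | 90% | 10% |

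An observed difference below about 1.96 × 0.615 = 1.2 kg ends the procedure, whatever the mediator shows.

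**Step 3. Detection with and without that step.** 3,000 trials were simulated per scenario, with 210 per arm and outcome SD 6.3 kg within arm. The article gives no path sizes, so these are assumptions: the intervention shifts the mediator by 0.3 or 0.5 SD, and 50% or 100% of the total effect is mediated. The mediator-to-weight slope is then (proportion × total effect) / shift; for example 1.0 × 0.7 / 0.3 = 2.3 kg per SD of mediator. Causal steps requires all three tests to be significant. The comparison requires only the arm-to-mediator and mediator-to-weight paths, and stands in for a direct test of the indirect effect.

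| Total effect | Mediated | Mediator shift | Causal steps | Two paths only |
|---|---|---|---|---|
| 0.7 kg | 50% | 0.3 SD | 17% | 85% |
| 0.7 kg | 50% | 0.5 SD | 13% | 63% |
| 0.7 kg | 100% | 0.3 SD | 19% | 86% |
| 0.7 kg | 100% | 0.5 SD | 21% | 99% |
| 1.0 kg | 50% | 0.3 SD | 34% | 86% |
| 1.0 kg | 50% | 0.5 SD | 33% | 91% |
| 1.0 kg | 100% | 0.3 SD | 35% | 87% |
| 1.0 kg | 100% | 0.5 SD | 38% | 100% |
| 2.0 kg | 50% | 0.3 SD | 82% | 87% |
| 2.0 kg | 50% | 0.5 SD | 90% | 100% |

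At 2 kg only 50% mediation was run. Full mediation with a 0.3 SD shift would need a slope of 2 / 0.3 = 6.7 kg per SD, which exceeds the outcome SD of 6.3 kg.

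The gain does not come from a looser error rate. If either path is truly zero, the two-path rule can succeed only by a false positive on that path, so its error is at most 5%.

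**Step 4. Measures held in one arm.** Where automaticity or transmitted weighing frequency is observed, arm is constant. The arm-to-mediator design matrix has rank 1 of 2, and the outcome model with arm and mediator has rank 2 of 3, so no indirect effect of randomised arm can be estimated. A model within the intervention arm relating weight change to weighing frequency and a second process measure has full rank (3 of 3) and can be fitted as an association.

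**The case against.** The article does not commit to causal steps. Structural equation modelling is offered beside it and can give the indirect effect with an interval. The process analyses are only described as likely, a logic model is still to come, and such detail commonly sits in a fuller plan. This lowers the weight of the point but does not remove it: the article itself names the weaker method, and no rule prevents its being chosen after the data are seen.

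At the effect the trial was sized for, little is lost. That stands. The 0.7 kg benchmark is also imperfect: it comes from a non-randomised nine-month comparison of a weaker intervention, and the pilot per-protocol difference was 3.0 kg. It serves only as an effect below plan that the protocol itself reports.

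Three stronger readings are tempting and are not supported:

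- A reader might infer that automaticity and the transmitting scales will enter the between-arm mediation model, where they could not be estimated. The article names no mediators and plans associations for these measures. The hypothesised mediator, cognitive restraint, is held in both arms, as is questionnaire weighing frequency.
- A reader might infer that mediator and weight come from the same visit, leaving their order open. Nothing says so, and restraint at three and six months precedes weight at 12 months.
- A reader might infer that the mechanism would probably be declared unsupported even if true. That needs both an effect well below 2 kg and the choice of causal steps. The article also plans analyses that need no significant total effect: between-arm differences in restraint and weighing frequency, the association between weighing and restraint, and dose–response.

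**Conclusion.** The point holds in limited form. The plan permits a mediation method that, in its classical form, depends on a significant total effect and does not quantify the indirect effect. The cost is large below plan: the first step alone fails in about 79% of trials at 0.7 kg and 63% at 1.0 kg. At 2 kg it fails in about 10%, and detection falls by roughly 5 to 10 percentage points in the scenarios run.

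The power figures rest on 210 completers per arm, SD 6.3 kg carried from nine to 12 months, and a two-sided 5% test without covariate adjustment. The detection rates rest also on the assumed mediator shifts and proportions mediated, and on no confounding between mediator and weight, which randomisation does not guarantee. The analysis is a tentative process analysis, and no primary or secondary outcome depends on it.

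**What to change.** Delete the Baron and Kenny option. State that the indirect effect will be estimated directly as a product of coefficients, within structural equation modelling or by regression, and reported with a bootstrap 95% confidence interval whether or not the total effect is significant.

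Name the mediators for the between-arm analysis from those measured in both arms: cognitive restraint and questionnaire-reported frequency of self-weighing. Take the mediator at three months and measured weight at 12 months, and adjust for baseline weight and the stratification factor.

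As a clarification only, say that automaticity and transmitted weighing frequency stay as associations within the intervention arm, as the article already describes them.

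The cost is a few sentences in the analysis plan. The data, visits and sample size do not change, and standard software is enough.

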### Serious adverse events requiring hospitalisation

We will summarise the occurrence of serious adverse events in each arm relating to bulimia, anorexia and self-harm due to body dissatisfaction that result in hospitalisation by percentages and 95 % confidence intervals.

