#### Week two and four calls

The telephone calls in weeks two and four will include a review of how participants are getting on compared to their target weight, the frequency of self-weighing and the recording of weight over the previous weeks. Those not weighing themselves daily will be asked about barriers to this and the telephonist will help with practical solutions/ideas and strategies of how they might overcome them. Participants will be further encouraged to self-weigh daily. The importance of using the weight record to compare their weight to their goal will be emphasised, as well as engaging in regular physical activity/healthy eating. The aim is to suggest to participants that daily weighing is a healthy habit to help them manage their weight and that they should adopt this for the rest of their life. Apart from these scheduled calls, participants are not able to telephone the call centre to receive further support.

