### Secondary outcomes

The proportion of participants in the intervention and comparator group who have regained less than 1 kg in weight at three and 12 month follow-up.The difference between groups in weight change from baseline to three months follow-up (i.e., end of behavioural support for weight maintenance).The cost to the NHS per kg, and per kg/m [2], of the additional weight loss maintained for the intervention compared to comparator group at 12 months, the cost per quality adjusted life years (QALY) during the intervention period and predicted lifetime QALYs gained.To assess the effects of the intervention on uncontrolled eating, emotional eating and weight preoccupation at three and 12 months follow-up.

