### Sample size

The standard approach to sample size calculation is to aim to detect a worthwhile intervention effect. This is difficult here because there is a linear relation between overweight and mortality (30 % increase per 5 kg/m [2]) [19]. This kind of intervention may be applied broadly in contexts outside of the specific behavioural intervention we propose here and in any case, even here, at its likely maximal intensity and cost, is likely to cost around £20 per person or less in public health practice. Even very small decrements in weight are likely to be cost effective if they are maintained throughout life. Consequently, instead of an approach where we specify a sample size based on a clinically important difference, we propose a sample size based on the likely size of effect we expect to achieve, a 2 kg difference in change in weight at 12 months. A total of 280 participants randomised to each group (n = 560) will be sufficient to detect a 2 kg difference in change in weight at 12 months follow-up between the intervention and comparator group, with 90 % power and 5 % significance level. This estimate is based on data from our pilot trial [13] where we found the standard deviation of the difference from baseline (i.e., end of weight loss/start of maintenance programmes) to nine months follow-up in those who lost at least 5 % of their starting weight was 6.3 kg. 560 participants allows for 25 % loss to follow-up at 12 months.

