### Analysis plan

The analyses will be conducted using the intention to treat principle. The primary outcome will be assessed by analysis of covariance to compare weight change (baseline to 12 months) between the groups. Thus the analysis uses weight at follow-up adjusted for baseline weight and adjusts for the baseline stratification factor, intention to maintain or continue weight loss, as is standard. All participants will be included in the primary analysis but those who are absent from follow-up will have final weight imputed. A similar analysis will be used to compare the secondary outcome of change in weight from baseline to three month follow-up.

The analysis of the proportion of participants in each group who regain no more than 1 kg from their weight at the end of the weight loss programme (i.e., successful maintainers) at three and 12 months follow-up will be conducted using generalised mixed modelling adjusting for the stratification variable. The results will be presented as odds ratios, 95 % confidence intervals and associated p values.

We have four pre-planned exploratory subgroup analyses, examining the effect of gender, initial weight loss programme, whether a person is intending to continue to attend their weight loss programme or not and whether a participant wished to lose or maintain weight. It is possible that different weight loss programmes teach people weight loss maintenance skills to a greater or lesser extent and therefore this could modify the effectiveness of the intervention. Gender may also influence the effectiveness of the intervention as previous research has found men lose more weight than females and have had less attempts at weight loss which could influence subsequent maintenance of weight loss [13, 23]. As some participants will wish to continue to lose weight or continue to attend their weight loss programme the intervention we propose here may not be as effective for those that are aiming to lose weight, we will explore whether there is support for this hypothesis.

The effects of the intervention on uncontrolled eating, emotional eating and weight preoccupation at three and 12 months will be investigated. Groups will be compared with repeated measures mixed modelling, adjusting for stratification variable. The results will be summarised as adjusted means and 95 % confidence intervals.

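### The only stated adverse-event summary counts eating disorders and self-harm only if they led to hospitalisation (and self-harm only with one motive), so non-admitted and unattributed cases are left out and a count of zero would say little about safety

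*Protocol article*

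**What the plan says.** In the protocol article, the section headed "Serious adverse events requiring hospitalisation" is the only place where adverse events are analysed. It promises a summary, arm by arm, that is restricted to events "relating to bulimia, anorexia and self-harm due to body dissatisfaction that result in hospitalisation by percentages and 95 % confidence intervals". The analysis is descriptive, with no test, margin or power claim.

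One other set of outcomes bears on harm. Secondary outcomes includes "To assess the effects of the intervention on uncontrolled eating, emotional eating and weight preoccupation at three and 12 months follow-up". For these scales, the Analysis plan says "Groups will be compared with repeated measures mixed modelling, adjusting for stratification variable", with results given as adjusted means and confidence intervals.

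On the intervention itself, the section on the week two and four calls describes the message that telephonists are meant to convey: "daily weighing is a healthy habit to help them manage their weight and that they should adopt this for the rest of their life".

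**The concern.** By naming bulimia, anorexia and self-harm, the article shows which harms of daily self-weighing it has in mind. It then sets conditions that an event must meet before it is counted. Every event must have resulted in hospitalisation, and self-harm must also have a particular motive. Three kinds of case therefore drop out although they are the harms of interest:

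- a new eating disorder managed by a general practitioner or an outpatient service;
- self-harm that did not lead to admission;
- self-harm that did lead to admission but has no body-dissatisfaction motive attributed to it.

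The stake is how the result will be read. The Discussion presents the intervention as simple, cheap and of wide potential reach, and the calls promote weighing as a lifelong habit. A line saying that no serious adverse events occurred could be taken as reassurance about eating disorders and self-harm in general, when it covers only the hospitalised part of them.

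**Working it through.** **1. The plan's own figure.** The adverse-event section contains no number to reproduce, so the check starts from the sample size: "A total of 280 participants randomised to each group (n = 560) will be sufficient to detect a 2 kg difference" in weight change at 12 months, "with 90 % power and 5 % significance level". With SD 6.3 kg, and 5% taken as two-sided, n per arm = 2 × (1.96 + 1.28)² × 6.3² / 2² = 209 after rounding up. Allowing for 25% loss, 209 / 0.75 = 279, against 280 stated. The figure reproduces and is not at issue. It gives 280 randomised per arm and about 280 × 0.75 = 210 followed to 12 months.

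**2. What the rule counts.**

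| Case | Counted as written? |
|---|---|
| Bulimia or anorexia, admitted | Yes |
| Bulimia or anorexia, managed outside hospital | No |
| Self-harm, admitted, attributed to body dissatisfaction | Yes |
| Self-harm, admitted, no such motive recorded | No |
| Self-harm, not admitted | No |

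**3. Expected counts.** The article gives no rate, so these are assumed rates of qualifying events per person over 12 months, equal in both arms. Expected total = 560 × p; chance of no event in either arm = (1 − p)^560.

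| Assumed p | Expected total | Chance of none |
|---|---|---|
| 0.05% | 0.28 | 76% |
| 0.1% | 0.56 | 57% |
| 0.2% | 1.12 | 33% |
| 0.5% | 2.8 | 6% |
| 1% | 5.6 | 0.4% |

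**4. What a zero would mean.** With no events among n, the exact two-sided 95% upper limit is 1 − 0.025^(1/n). For n = 280 it is 1.3%; for n = 210 it is 1.7%. If one arm has no events, the other needs six of 280 to reach two-sided Fisher p < 0.05 (5 v 0 gives p = 0.061; 6 v 0 gives p = 0.030).

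**5. How the hospitalisation condition thins the count.** Suppose 2% of the intervention arm suffered one of these harms and 10% to 20% of those were admitted (both assumed). The qualifying rate is then 0.2% to 0.4%. Expected counted events in the arm are 280 × 0.002 = 0.56 to 280 × 0.004 = 1.12, with a 57% to 33% chance of none. If instead all 2% qualified, 280 × 0.02 = 5.6 events would be expected and the chance of none would be 0.98^280 = 0.3%.

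**6. Whether the scales fill the gap.** In SD units, and ignoring any gain from covariate adjustment, the 95% half-width for a difference in means with 210 per arm is 1.96 × √(2/210) = 0.19. The detectable difference at 80% power is (1.96 + 0.84) × √(2/210) = 0.27. If 2% of an arm worsened by 2 SD, the mean would move 0.02 × 2 = 0.04 SD, well inside the half-width. If 10% did, it would move 0.10 × 2 = 0.20 SD, about equal to it. The scales can show a general shift. They do not identify a few clinical cases, and none of the three named scales is a record of self-harm.

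**The case against.** The strongest reply is that harm is not monitored by this table alone. Uncontrolled eating, emotional eating and weight preoccupation are secondary outcomes in both arms at three and 12 months, without any hospitalisation condition and with reasonable power for a moderate shift. Process measures adds coded open-ended questions on weight control practices in both arms at three, six and 12 months. This stands in part: these measures narrow the gap, but they do not diagnose an eating disorder or set out to record self-harm.

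A second reply is that the precision limits in steps 3 and 4 come from 280 per arm and would apply to any rare category. That also stands. Broadening the definition would raise the counts by an amount that the article does not allow one to calculate, and it would not make the trial powered for rare harms.

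Three stronger readings are tempting, and the document does not support them:

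- **That the table will be near zero whatever the intervention does.** This needs an event rate, and none is given. At an assumed 2% qualifying rate, 5.6 events would be expected in the arm.
- **That deaths and other serious events are excluded from the trial.** The section states what will be summarised, not everything that is collected. General reporting of deaths and serious events is commonly left to the full protocol, and its absence from an article shows nothing.
- **That the motive qualifier makes someone judge whether the intervention caused the event, with bias from knowing the arm.** The qualifier describes why a person self-harmed, and it applies to one of the three event types. The article does not say who classifies events or whether they are blinded, so bias is conjecture.

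**Conclusion.** The point holds as a limited criticism of a stated rule. The only adverse-event comparison in the article leaves out non-admitted eating disorders, non-admitted self-harm and admitted self-harm without the attributed motive, and no other stated outcome records these cases individually.

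That the cases are left out follows from the text and needs no assumption. The size does rest on assumption. At qualifying rates of 0.05% to 0.2%, about 0.3 to 1.1 events are expected in 560 participants, and 0 of 280 excludes only rates above about 1.3%. The share of these harms that leads to admission is not in the document, so how many cases the rule misses cannot be stated. What can be said is that a finding of no events under this rule would be weak evidence of safety and should not be reported as more. The primary outcome and the sample size are unaffected.

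**What to change.** In the serious adverse events section, remove hospitalisation and the body-dissatisfaction motive as conditions for counting. Summarise by arm:

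- any reported new diagnosis or treatment of an eating disorder, in any care setting;
- any reported self-harm, whether or not it led to admission.

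Keep the present set (hospitalised, with the motive qualifier for self-harm) as a subset of these. Ask the same questions in both arms in the existing three-, six- and 12-month questionnaires. Identical questioning matters because only the intervention arm has the telephone calls, which give extra chances to mention a problem. The choice of interval method and denominator can be left to the statistical analysis plan.

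The cost is a wording change, a few items in questionnaires that both arms already receive, some unrelated events to record, and a table that looks less favourable. Because rare harms will remain beyond the trial's power, the report should give the upper confidence limit alongside any zero count.
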